### Patient and public involvement

There were no patients or members of the public involved in the planning of this study.

### Confounding variables

There is limited evidence for the relationship between physical activity and previously known determinants of outcomes following ICH. However, several factors may confound or mediate the potential impact of physical activity. The covariates included as potential confounders in this study are based on theoretical reasoning, and current evidence. The relationship between prestroke physical activity and the main groups of confounders is portrayed in figure 1.

**Figure 1 F1:**
[figure not shown]
Directed acyclic graph for confounders to the effect of physical activity on outcomes after intracerebral haemorrhage (stroke severity and poststroke mortality). Solid lines indicate the relationships between covariates, and the dotted line indicate the causal effect of physical activity.

Degenerative vascular changes are frequent in the ageing population. In addition to being a risk factor for all stroke, higher age has been identified as an important predictor of disability, and decreased long-term survival in ICH^33 34^ A person’s age also influences the probability of being physically active,^35^ and should therefore be considered a confounding factor. Sex, however, did not significantly influence the severity of haemorrhagic stroke in a meta-analysis of eight population‐based stroke incidence studies.^36^

Socioeconomic status-related differences influence haemorrhagic stroke severity, but could partly be explained by differences in comorbidities, disparity in health and care services, ethnicity, stress, job strain and life style factors. Income, education and living alone have been associated with mortality following the acute phase of stroke.^37^ Low income was found to increase the absolute risk of death at 3 months after ICH, and the effect was largely mediated by initial stroke severity.^38^ In adulthood, socioeconomic variables are associated with the propensity of being physically active.^39^ Among young people, a recent study found that haemorrhagic stroke survivors of African and Hispanic ethnicity have better outcomes compared with those of Caucasian descent.^40^ In the current study, country of birth will be used as a surrogate measure for ethnicity.

Active cigarette smoking has been associated with increased stroke severity,^41 42^ and premorbid alcohol consumption has been identified as independent determinant of functional status and mortality after ICH.^43^ Cigarette smoking and physical activity are intuitively incongruent behaviours, and both positive and negative associations has been described.^44^ Likewise, alcohol consumption has in some studies been found to be a contributor to sedentary behaviour.^45^

Patients with severe comorbidity may experience worse outcomes following ICH, although this has not been thoroughly investigated. One study found that dialysis patients with a medical history of stroke, diabetes and malignancy had a higher risk of mortality following ICH.^46^ In another study, global comorbidity evaluated by the Charlson Comorbidity Index was associated with increased risk of 90-day mortality, but not with the length of hospital stay, among immobile patients below 50 years of age.^47^ Severe disease may limit a person’s ability to be physically active, and thereby confound the effect of prestroke physical activity on outcomes following ICH.

Psychiatric comorbidity has been associated with stroke severity and functional outcomes in a population with both haemorrhagic and ischaemic stroke cases.^48^ Physical activity decrease the risk of depression, and a majority of people with depression report sedentary behaviour.^49 50^ Similarly, patients with psychotic diseases, such as Schizophrenia, generally have a very low level of physical activity.^51^

Hyperglycaemia and diabetes have been related to worse outcomes after ICH. Diabetes and high blood glucose in nondiabetic patients have been associated with cerebral complications, and are independent predictors of 30-day mortality, and 3-month mortality following ICH.^52^ Hyperglycaemia has also been found to decrease short term survival after ICH.^53 54^ The presence of hyperglycaemia in severe stroke may, however, be a result of an extensive cerebral lesion, causing a phycological increment of cortisol and catecholamines. Regular physical activity promotes blood glucose control in diabetic patients.^55^ Still, a large survey of the US population found that diabetic adults generally engaged in less physical activities compared with non-diabetic adults.

Atrial fibrillation is present in about one third of patients 3 months after ICH,^56^ and premorbid atrial fibrillation has been found to predict a higher risk of death 3 months after ictus.^57^ However, the risk increment seemed to be mediated by the higher prevalence of antithrombotic treatment in the group with atrial fibrillation. There is a complicated relationship between physical activity and the risk of atrial fibrillation. While a moderate amount of physical activity is protective for atrial fibrillation, vigorous physical activity increase the risk of atrial fibrillation in men.^58^

Coagulopathy caused by anticoagulants increase the risk of haematoma expansion, mortality and disability after ICH. Warfarin usage has been associated with increased risk of in-hospital haematoma expansion,^59^ and a doubled risk of mortality at 3 months after ICH.^60^ In an international multicentre pooled analysis, haemorrhagic volume on admission, haematoma expansion, functional status at discharge and 90-day mortality were similar in patients treated with warfarin and non-vitamin K antagonist oral anticoagulation (NOAK), meaning that the risk increment is substantial for treatment with NOAK as well.^61^ The propensity of being physically active may be connected to anticoagulant treatment through differences in the prevalence of atrial fibrillation and previous strokes.

The use of lipid-lowering drugs has been controversial in patients with ICH as hypocholesterolaemia has been identified as a risk factor for ICH and haematoma expansion.^62 63^ Low levels of serum lipids were also independently associated with a poor 3 months prognosis after ICH in women.^64^ The use of statins has, however, only been correlated to an increased risk of ICH in patients with a prior haemorrhagic or lacunar ischaemic stroke. On the other hand, several observational studies have reported better outcomes after ICH among patients medicated with statins. Premorbid statin usage was associated with a better long-term outcome at 12 months after ICH.^65^ Another study found that statins reduced mortality and disability without any negative effect on haematoma growth, but the association disappeared when adjusted for potential indication bias.^66^ Regular physical activity positively alter the levels of blood lipids, and may thereby decrease the probability of receiving statin treatment.^67^

A previous stroke or transient ischaemic attack (TIA) can potentially precondition the brain to endure ischaemia, and having gone through a TIA has been associated with lower ischaemic stroke severity.^3^ Although ischaemic tolerance may play an important role in haemorrhagic stroke severity, the influence of a preceding stroke or TIA has not yet been evaluated. Patients diagnosed with stroke or TIA are, however, likely to receive recommendations regarding physical activity in accordance poststroke guidelines.

In conclusion, the following potential confounders will be collected, and adjusted for: age, ethnicity, income, educational level, comorbidity, medical treatments, alcohol related disorders, drug abuse and smoking. The comorbidities accounted for are prior TIA, prior stroke, diabetes, psychiatric disorders and Charlson Comorbidity Index. The medical treatments accounted for are anticoagulant treatment, antihypertensive treatment, antiplatelet treatment and statin treatment.

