**Methods and analysis:**

This is a statistical analysis protocol for a matched cohort study, including all adult patients with intracerebral haemorrhage, and matched ischaemic stroke controls, treated at Sahlgrenska University Hospital in Sweden between 1 November 2014 and 30 June 2019. All patients have been identified in the Väststroke register, and the data file has been sent for merging with national registries. The follow-up of time for survival will be approximately 2–7 years. The sample size calculation indicates that a minimum of 628 patients with intracerebral haemorrhage is needed for power of 80% at an alpha level of 0.01. Multiple imputation by chained equations will be used to handle missing data. The entire cohort of patients with intracerebral haemorrhage will be matched with consecutive ischaemic stroke controls (1:3 ratio) using nearest neighbour propensity score matching. The association between prestroke physical activity and admission stroke severity will be evaluated using multivariable ordinal regression models, and risk for all-cause mortality will be analysed using multivariable Cox proportional-hazards models. Potential confounders include age, ethnicity, income, educational level, comorbidity, medical treatments, alcohol-related disorders, drug abuse and smoking.

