### Propensity scores and matching

To achieve equipoise between patients with ICH and ischaemic stroke, propensity score matching will be applied. We will include the entire cohort of patients with ICH and match them with consecutive ischaemic stroke patients, in a 1:3 ratio. The propensity score will be based on sex and potential confounding variables. The rational for the selection of confounders is given below. Here, we assume that confounders for the effect of physical activity on stroke severity will be analogous for ICH and ischaemic stroke. We will conduct generalised boosted regression modelling to calculate the propensity scores.^26^ We intend to estimate the average eﬀect of being physically active, that is, the average treatment effect for the treated will be applied. The number of trees, shrinkage and interaction depth will be tuned by using 10-fold cross-validation. We will use the stopping rule es.mean, which uses the absolute standardised bias as balance metric and the mean of the covariate balance metrics to summarise across variables. The propensity score matching will be conducted using the nearest neighbour matching method, with a logistic distance measure and without replacement.^27^

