### Regression models

We will conduct separate models for haemorrhagic and ischaemic stroke cases, respectively. All models will be adjusted for potential confounders. The association between prestroke physical activity and admission stroke severity will be evaluated using multivariable ordinal regression models.^28^ For the ordinal regression, NIHSS scores will be trichotomised. A subgroup analysis will be performed for patients with first-time ICH. Prior to the analyses, absence of multicollinearity, and the proportional odds assumption will be checked. Diagnostics will be performed using surrogate residuals.^29^

The association between prestroke physical activity and all-cause mortality will be evaluated using multivariable Cox proportional-hazards models.^30^ Additional models will be fitted adjusted for admission stroke severity.^31^ Model diagnostics will be applied to evaluate violations of the proportional hazards assumption, random censoring and functional forms of continuous covariates.^32^ Furthermore, outlying and influential observations will be checked for all models.

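### Sex is collected and used in the stroke-type matching but is absent from the covariates listed for the outcome models, and nothing in the plan justifies this for mortality

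*Protocol article*

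**What the plan says.** Four places in the protocol article bear on this.

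- **Table 1** lists sex (female/male) among the variables from the Väststroke register, so it is in hand.
- **Propensity scores and matching** names sex apart from the confounders: "The propensity score will be based on sex and potential confounding variables". The purpose is stated as "To achieve equipoise between patients with ICH and ischaemic stroke, propensity score matching will be applied". The same section assumes that confounders of the activity–severity relation are the same kind in both stroke types.
- **Regression models** says "We will conduct separate models for haemorrhagic and ischaemic stroke cases, respectively" and "All models will be adjusted for potential confounders". It specifies ordinal models for severity, a first-time ICH subgroup analysis, Cox models for all-cause mortality, and further models that add admission severity.
- **Confounding variables** accepts age as a confounder because it predicts outcome and influences activity. The next sentence turns to sex: "Sex, however, did not significantly influence the severity of haemorrhagic stroke". The section closes with what will be collected and "adjusted for: age, ethnicity, income, educational level, comorbidity, medical treatments, alcohol related disorders, drug abuse and smoking", then itemises the comorbidities and treatments. Sex is in none of these. The abstract repeats the main list: "Potential confounders include age, ethnicity, income, educational level, comorbidity, medical treatments, alcohol-related disorders, drug abuse and smoking".

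**The concern.** Read together, these sections put sex in the matching step and leave it out of every model that estimates an effect of activity. The single remark on sex reports a non-significant association with one outcome in one stroke type. A non-significant association does not show that a variable is not a confounder. It also cannot speak to survival over roughly 2–7 years, which is a separate objective with its own models. The other half of the confounding question, whether active and inactive patients differ in sex, is not discussed, although the plan does discuss it for age.

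At stake is avoidable confounding of the activity estimates, chiefly the mortality hazard ratios. It also bears on the plan's claim of comprehensive covariate adjustment, since sex is a basic baseline variable that readers will look for.

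**Working it through.** **No figure of the plan to reproduce.** The documents give no sex distribution by activity level and no sex–outcome ratio. The sample size of 628 does not depend on sex adjustment.

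**Step 1: is sex in the outcome models?** The models are adjusted for the potential confounders (Regression models). The potential confounders are listed at the end of Confounding variables, without sex. The matching section's phrase, sex plus the potential confounding variables, places sex outside that group. As written, sex is not a covariate in any ordinal or Cox model.

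**Step 2: does the matching make up for it?** Matching sets ICH against ischaemic stroke. Each model compares active with inactive patients inside one stroke type.

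- The whole ICH cohort is kept, so matching changes nothing in the ICH models.
- In the ischaemic group, matching aims at the overall sex mix of the ICH group, not the mix within each activity level. Take the plan's expected 60% inactive, and assume 62% men among active and 47% among inactive patients. The overall share is 0.4 × 0.62 + 0.6 × 0.47 = 0.248 + 0.282 = 0.53. A matched group with 53% men at both activity levels has the same overall share. Equal totals therefore do not imply balance by activity.

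**Step 3: which models does the remark on sex reach?**

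| Model | Rationale on sex in the plan |
|---|---|
| Severity, ICH (including first-time ICH) | Non-significant meta-analysis result |
| Severity, ischaemic | Same result, carried over by the stated assumption of analogous severity confounders |
| Mortality, ICH | None |
| Mortality, ischaemic | None |

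**Step 4: possible size, under assumptions.** Let p1 and p0 be the proportions of men among active and inactive patients, and H the mortality hazard ratio for men. All three are assumed. The approximate factor by which omitting sex multiplies the activity hazard ratio is

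B = [1 + p1(H − 1)] / [1 + p0(H − 1)]

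- p1 = 0.60, p0 = 0.50, H = 1.2: B = 1.12 / 1.10 = 1.018
- p1 = 0.62, p0 = 0.47, H = 1.5: B = 1.31 / 1.235 = 1.061

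A wider grid (50% men among inactive, 55–65% among active, ratio 1.2 to 2.0) gives B from 1.009 to 1.10. With no sex difference between activity groups B = 1. With the proportions reversed it falls below 1: 1/1.018 = 0.982 to 1/1.061 = 0.943.

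**Step 5: direction.** If active patients are more often men and men die sooner, B exceeds 1. An illustrative true hazard ratio of 0.50 would appear as 0.50 × 1.018 = 0.51 to 0.50 × 1.061 = 0.53, closer to 1.

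**The case against.** Several points on the other side have force.

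- **Exclusion and motive are not stated outright.** No sentence says that sex is left out of the models. The abstract's list is worded openly, and the causal diagram is not shown. The list in Confounding variables nevertheless reads as complete and says what will be adjusted for. The article presents itself as the statistical analysis plan, so this is not a detail left to another document. The omission stands. A reader might go further and infer that sex was dropped because of the non-significant result. The text does not say so: it reports the result and draws no conclusion from it.
- **Ischaemic severity is not without a rationale.** A reader might infer that the haemorrhagic evidence is applied to ischaemic stroke without comment. The matching section states the assumption that bridges the two. One may doubt it, but it is there. It is limited to severity and does not reach mortality.
- **The bias may be small or absent.** The inputs are assumed. The formula uses crude proportions and is approximate for a hazard ratio. The models already adjust for smoking, alcohol-related disorders, drug abuse, income and comorbidity, which may absorb part of any sex difference. This stands in full. The plan's passing remarks on atrial fibrillation in men and on lipids in women do not show that sex confounds activity and death.
- **A spurious benefit does not follow.** A reader might infer that omitting sex would manufacture a protective effect. Under the assumed inputs it would dilute one. The opposite requires proportions or a sex effect in the other direction, and the documents support neither.

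**Conclusion.** The point holds as a gap in the listed covariates. Sex is available and used for matching, but it is absent from the adjustment set of the outcome models, and the matching does not replace that adjustment. The severity models have a thin rationale: a non-significant result, extended to ischaemic stroke by assumption. The mortality models have none.

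The documents do not allow the bias to be sized. Under the main assumed inputs it is about 2–6% on the hazard ratio, towards the null for a protective effect. Other assumptions make it zero, larger or opposite in sign. This is a modest improvement to the plan; it does not show that the planned conclusions would be wrong.

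**What to change.** Add sex to the list of covariates at the end of Confounding variables and to the matching list in the abstract. State in Regression models that it enters:

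- the ordinal severity models for ICH, ischaemic stroke and first-time ICH;
- the Cox mortality models for ICH and ischaemic stroke, both with and without admission severity.

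If the authors prefer to leave it out, they should justify that separately for each outcome and stroke type, on grounds other than non-significance.

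The cost is one sentence and one degree of freedom per model. No new data are needed, and the sample size calculation is untouched.

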### Ethics

Data collection for the PAPSIGOT project was approved by the Regional Ethical Board of Gothenburg on 4 May 2016 (346-16). An additional application was approved by the Swedish Ethical Review Authority on 7 July 2021 (2021-03324). Research within the framework of quality registers does not require written informed consent from included patients. The Personal Data Act (Swedish law #1998:204, issued 29 April 1998) allows data from medical records to be collected for quality control without receiving a written informed consent.
